# Effects of programmed flexor–extensor alternating electrical acupoint stimulation on upper limb motor functional reconstruction after stroke: study protocol for a double-blind, randomized controlled trial

**DOI:** 10.1186/s13063-023-07283-3

**Published:** 2023-05-11

**Keywords:** Stroke sequelae, Upper limb motor dysfunction, Programmed, Flexor–extensor, Acupoint, Electrical stimulation

## Abstract

**Background:**

Stroke’s prevalence and morbidity are increasing (Guano, et al. Neuro 89:53–61, 2017), and limb motor dysfunction is left in most patients (Gittler, et al. JAMA 319:820–821, 2018). Particularly, the rehabilitation of upper limbs is more difficult and time-consuming (Borges, et al. The Cochrane database of systematic reviews 10:CD011887, 2018).

**Methods:**

A double-blind randomized controlled trial (RCT) will be conducted to investigate whether a new functional electrical stimulation (FES) combined with acupoint therapy is more effective in the rehabilitation of upper limb motor dysfunction after stroke. Patients who meet the inclusion criteria will be randomly divided into two groups: programmed flexor–extensor alternating electrical acupoint stimulation group (PES group) and conventional flexor–extensor alternating electrical acupoint stimulation group (CES group), which will be treated for 3 weeks. The primary outcome measures are electroencephalogram (EEG) and surface electromyogram (sEMG). The secondary outcome variables include MBI (modified Barthel index), China Stroke Scale (CSS), FMA-U (Fugl-Meyer assessment upper limb), MMT (manual muscle testing), and Brunnstrom.

**Discussion:**

The results of this study are expected to verify the efficacy of PES therapy in the rehabilitation of upper limb motor function after stroke. This may promote the widespread use of the therapy in hospitals, communities, and homes for early and continuous treatment.

**Trial registration:**

ClinicalTrials.gov NCT05333497. Registered on April 11, 2022.

## Introduction

Global Burden of Disease (GBD) has indicated that stroke is the leading cause of death and disability among adults in China [1]. More than 80% of patients have suffered from acute motor dysfunction, and over 50% have long-term limitations [2]. Among them, about 69 to 80% of stroke patients have upper limb motor dysfunction [3]. During the recovery, the affected upper limb shows a flexion pattern and limited movement, which seriously influences the patient’s daily life. It is a key and difficult point of stroke sequela always, and a lot of exploration of different rehabilitation therapies and intervention effects has been conducted by domestic and foreign scholars. With the increasing recognition of traditional Chinese medicine (TCM), especially acupuncture, the therapies for stroke sequelae by integrated traditional Chinese and Western medicine have been widely used. In recent years, functional electrical stimulation (FES) has been a concern in the rehabilitation field. Therefore, the combination of FES and TCM acupoint therapy on upper limb functional reconstruction after stroke is worth further study.

FES is commonly used in patients with motor disorders such as stroke, spinal cord injury, and hemiplegia. The possible mechanism is mainly brain remodeling and activity-dependent plasticity [4]. By electrical stimulation, one or more groups of muscles are induced to generate muscle movement or mimic normal voluntary movement in order to improve the function of the stimulated muscles or muscle groups. Studies have shown that FES can help patients with neural dyskinesia rebuild some motor function [5] to achieve the purpose of rehabilitation, and can also help relieve muscle pain and spasm for the improvement of muscle status [6]. It has been widely used in the rehabilitation of hemiplegia patients and has very definite effects on the recovery of sensory and motor function of limbs.

Acupuncture is a vital part of TCM, as well as an internationally recognized physical therapy, with high safety, significant efficacy and no serious adverse events in limb motor rehabilitation after stroke [7]. Currently, the mechanism of an acupoint is not completely clear, but the viewpoint of central nervous control is an essence of the curative effect [8–11]. In this study, the flexor–extensor alternating electrical acupoint stimulation instrument has combined traditional acupuncture with modern low-frequency technology, with the advantage of non-invasion and convenience, to improve joint activity, relieve spasm, enhance muscle strength, and promote the central nervous system and limb function reconstruction [12]. However, simultaneous movement of several single joints is produced by local stimulation with the conventional instrument, but no coordinated movement of multiple joints is generated. In order to improve patients’ ability of daily living (ADL), the program is improved in this study based on the original instrument to a programmed one. Through the output of electrical stimulation at different times, muscles or muscle groups in different parts are stimulated to form programmed movement. By neuro-electrophysiological test and scale evaluation, this study will conduct a double-blind RCT to objectively evaluate the effect of flexor–extensor alternating electrical acupoint stimulation on upper limb motor functional reconstruction.

## Methods

### Pre-design

Five healthy subjects and five patients are selected to conduct a survey on the comfort of this instrument parameters, body position, stimulation time, muscle fatigue, completion of programmed movements, and other conditions and to refine the trial design in response to feedback and comments from participants.

### Study design

This clinical trial is designed as a double-blind RCT with 90 participants (60 stroke patients and 30 healthy controls) to be recruited. SPIRIT checklist and CONSORT statement were used when writing this study protocol [13, 14]. The whole study duration is about 17 weeks, including the washout period (7 days), the screening observation (3–7 days), the treatment period (3 weeks), and the follow-up period (3 months) (Fig. 1). After signing the informed consent (version date: 2021.11.19, version number: V1.1), all patients will be randomized divided into two groups in a blind manner—programmed flexor–extensor alternating electrical acupoint stimulation group (PES group) and conventional flexor–extensor alternating electrical acupoint stimulation group (CES group) with 30 cases in each, and the treatment will last for 3 weeks (6 days of treatment with 1-day rest per week). Healthy controls are used as a baseline without treatment. Participation in the trial is entirely voluntary, and they can withdraw at any time during the study without any reason. The participants are blinded, and the signal acquisition, evaluation, and outcome assessors are blinded. Because the treatment operation is too programmed, it is difficult to blind the performers. To prevent unblinding, subjects are advised not to discuss treatment options with evaluators (Figs. 2 and 3). All the patients will be followed up for 3 months. The follow-up time points will be at the end of the 1st month and 3rd month after the trial. The data and results will be monitored by the Data and Safety Monitoring Committee (DSMC) and the Ethics Committee.

**Fig. 1 Fig1:**
[figure not shown]
Flow diagram of the whole trial (details of patients’ and healthy controls’ groups in Figs. 2 and 3)

**Fig. 2 Fig2:**
[figure not shown]
Flow diagram of the PES group and CES group. MBI, Modified Barthel Index; CSS, China Stroke Scale; U-FMA, upper Fugl-Meyer motor function assessment; MMT, Manual Muscle Testing; Brunnstrom, Brunnstrom motor function assessment

**Fig. 3 Fig3:**
[figure not shown]
Flow diagram of the healthy control group

### Study setting

The patients are stroke inpatients meeting the inclusion criteria in Acupuncture and Moxibustion Ward 3 of the Second Affiliated Hospital of Heilongjiang University of Chinese Medicine in Harbin, China. This hospital is the highest level one in China.

### Patients and healthy controls

All the 60 eligible patients will be recruited through clinic centers, hospital announcements, and China’s pubic social network platform (*WeChat* application), and the enrollment time is expected to be 3–5 months. After being informed of the possible problems during the participation in this trial, they should sign the informed consent and will be assessed by sEMG [15], resting state EEG with closed eyes [16], and scales. And the patients will be randomly assigned to either group. All patients will receive conventional medication, rehabilitation, and acupuncture. As informed, during the study period, any other Chinese and Western medicine or treatment care related to this disease will not be permitted without the approval from the trial staff in advance.

The healthy controls only need the detection of sEMG and EEG. Neither patients nor healthy controls will be involved in the design, conduct, or data processing of this study. The inclusion criteria and exclusion criteria of patients and healthy controls are presented in Table 1.

**Table 1 Tab1:** The inclusion criteria and exclusion criteria

Inclusion criteria	Exclusion criteria
**Inclusion criteria for patients**	
a. Meet the diagnostic criteria of stroke [15, 16]	a. Severe cognitive dysfunction, severe aphasia, cannot cooperate with the whole treatment or testing process
b. Age: 35 ~ 75 years old, male and female	b. Patients with serious primary diseases such as heart, lung, kidney, liver, and endocrine system
c. Course of disease: 2 weeks to 3 months after stroke, stable vital signs, basically normal cognitive function, can cooperate to complete the test	c. Neurological or musculoskeletal diseases affecting functional recovery before onset
d. Manual muscle test (MMT) ≥ 2 [17], modified Ashworth (MAS) [18] of paralyzed upper limbs are graded I ~ II	d. Cerebral stem stroke or bilateral stroke
e. Body mass index (BMI) ≤ 28	e. Patients with severe anxiety, depression, affective disorders, schizophrenia, and other serious mental disorders
f. No serious heart, lung, kidney, and other functional damage; serious underlying diseases; pain in the affected side of the upper limb joint	f. Examination confirmed by brain tumor, brain trauma, brain parasitic diseases, metabolic disorders, rheumatic heart disease, coronary heart disease, and other heart diseases with atrial fibrillation caused by cerebral embolism
g. The informed consent is signed by the patient and/or his/her family members. Note: patients who meet the above 7 criteria can be included in this study	g. Patients with skin damage, infection, or deformity at the treatment site

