### Randomization and blinding

A random grouping method will be adopted. The SPSS 26.0 statistical software is used to randomly generate serial numbers and groups, and blind selection cards are made and put into envelopes (with no difference in appearance). Numbers are according to the inclusion sequence of the subjects, and corresponding experimental groups are entered according to the blind selection cards. Envelope administrators will not participate in this study, and the staff who generate the allocation sequence, enroll participants, and assign participants to interventions will be different ones without communication about the allocation. When patients are treated, the operators should follow the treatment assignment.

The study will be conducted in a double-blind method. Due to the particularity of the operation, the operators (participating doctors and physiotherapists) will not be blinded, but only the electrophysiological indicator collectors, scale evaluators, data recorders, statistical analysts, outcome assessors, and the included subjects are blinded. The operators are not involved in the design of the protocol; thus, they have no determination of the potential differences of each treatment method. They only need to ensure the protocols are followed accurately, so that the treatment and results will not be influenced even though they are unblinded.

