### Measurement

*Patient demographics*: age, gender, BMI, course of disease, functional damage and serious underlying diseases, and date of admission.

*Healthy control demographics*: age, gender, BMI, once eyes-closed resting state EEG signals, and real-time sEMG signals.

*Treatment information*: enrollment time, treatment time, hospital discharge time, withdrawal time, problems in the treatment period, scale evaluation (MBI, CSS, FMA-U, MMT, and Brunnstrom), eyes-closed resting state EEG signals, and real-time sEMG signals [19].

*Follow-up*: dates of follow-up visit, adjuvant therapies, overall health status at and during follow-up (recovery condition of the upper limb, activity of daily living, fundamental diseases, drugs, death, loss of follow-up), and scale evaluation (MBI, CSS, FMA-U, MMT, and Brunnstrom). The follow-up staff will also be blinded.

The trial time enrollment schedule is estimated to be 6–8 months with a 3-month follow-up after the end of treatment. In 48 h after signing the informed consent, the patients will be randomly divided into groups according to the order in the clinic and then receive treatment after being evaluated (Table 3).

**Table 3 Tab3:** Schedule of study procedures

**Study period**	**Washout**	**Observation**	**Baseline**	**Treatment**			**Follow-up**	
Timepoint	≦7 days	3-7 days	0 day	1 day*	3 week◈	3 week^⊙^	1 month	3 month

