##### Data statistical analysis

The SPSS 26.0 statistical software will be used for analysis by three-party statisticians. Data presentation: each measurement is presented as mean ± standard deviation if it conforms to a normal distribution, or median and quartiles if it does not. Intra-group comparisons: if the measurement data in each group conforms to a normal distribution, paired *T* test will be used for comparison between each group before and after treatment; if all data does not conform to a normal distribution, paired sample Wilcoxon rank sum test is used. Inter-group comparison: If the measurement data of conforms to a normal distribution, one-way ANOVA will be performed, and the LSD method will be used for comparison between the groups (Welch’s test will be used to correct Dunnett’s T3 method when the variance is not equal); if the data does not all conform to a normal distribution, non-parametric test will be performed (Mann–Whitney *U* method is applied for comparison between two groups, and Kruskal–Wallis *H* method is for comparison between multiple groups).

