## Discussion

In the process of motor function recovery in stroke patients, flexor and extensor coordination disorder is a common symptom [26, 27]. At present, the theoretical basis of limb function rehabilitation of apoplexy mainly includes brain plasticity theory and limb movement control theory [28]. Patients show the spasticity pattern of the upper limb flexor and lower limb extensor [29]. Therefore, stimulation of the flexor or extensor muscle alone is not enough. Abnormal movement patterns can affect the recovery of motor function and cause wrong posture, which needs to be corrected timely.

Rehabilitation of the upper limbs is difficult and time-consuming. This instrument is combined with the advantages of FES and acupoints. By stimulating the corresponding acupoints of the active and passive muscle groups of the upper extremity at low frequency, the contractile ability of the muscles is enhanced, and the relaxation and contraction function of the active and antagonistic muscle groups is coordinated, to effectively improve the motor function of the affected limb and promote the recovery of the central nervous system.

Six months is a gold period for rehabilitation after stroke [30]. But due to the COVID-19 epidemic, treatment has affected many patients. Rehabilitation training should be initiated soon after the stroke condition stabilized for better recovery effect [31]. The instrument is portable, easy to use, non-invasive and painless, and low cost, which may be easy to be accepted at home or in the community.

This study is a double-blind RCT. The safety and efficacy of the instrument are beyond doubt after 20 years of clinical application and many clinical studies [32–34]. This study improved the previous electrical stimulation output strategy, formed into a programmed one. Through the evaluation of neuro-electrophysiology and scales, the curative effects will be visualized and objectified for better interpreting the difference in the two stimulation methods, which may provide a new reference for integrated traditional Chinese and Western medicine in the treatment of motor function recovery after stroke.

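### The PES–CES comparison ignores time since stroke, which is recorded and ranges from 2 weeks to 3 months at entry, and so gives up precision that could be had at almost no cost

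*Protocol article*

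**What the plan says.** Inclusion criterion c for patients in Table 1 reads "Course of disease: 2 weeks to 3 months after stroke, stable vital signs". Under Measurement, the baseline items for patients are "age, gender, BMI, course of disease, functional damage and serious underlying diseases, and date of admission", so time since stroke is collected.

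The Discussion states that "Six months is a gold period for rehabilitation after stroke" and adds that training should begin soon after the patient is stable. The article thus treats time since stroke as relevant to recovery, and the whole entry window lies inside the period it singles out.

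Under Randomization and blinding, "The SPSS 26.0 statistical software is used to randomly generate serial numbers and groups", and "Numbers are according to the inclusion sequence of the subjects". No balancing factor is named.

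Under Data statistical analysis, normally distributed data are compared between groups as follows: "one-way ANOVA will be performed, and the LSD method will be used for comparison between the groups", with a Welch/Dunnett T3 variant for unequal variances. Other data go to the Mann–Whitney test for two groups or the "Kruskal–Wallis" test for several. None of these tests takes a covariate.

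**The concern.** The latest permitted entry is more than six times as long after stroke as the earliest (about 90 days against 14). If expected change over the 3-week treatment depends on where a patient stands in that window, mixing early and late entrants adds variation to both arms. An unadjusted test leaves all of that variation in its error term.

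With 30 patients per arm, one allocation can also place noticeably earlier patients in one arm. Without a prespecified adjustment, the team would then have to choose between reporting a result it suspects is shifted and adjusting after seeing the data. Adjusting for the baseline value of the outcome alone need not settle this, because two patients with the same baseline score at 2 weeks and at 12 weeks may have different prospects.

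**Working it through.** **Inputs from the article.** Entry window 2 weeks to 3 months, taken as 14 to 90 days. From Sample size estimation: effect size 0.8, alpha 0.05, power 0.80, 25 per group evaluable, 30 per group randomised. Pretest differences from the healthy group are 167.61 and 68.17, with SDs 127.22 and 148.46.

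**Assumptions.** Entry times are uniform over the window. The correlation r between time since stroke and the outcome within arm is 0.2 to 0.5. The article gives neither.

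**1. The plan's own figure.** With two-sided alpha, n per group = 2 × (1.960 + 0.842)² / 0.8² = 24.5, so 25. This matches. Power at 25 per group by the same normal approximation is Φ(0.8 × √(25/2) − 1.96) = Φ(0.868) = 0.807 (0.791 with the t distribution).

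**2. Chance imbalance in time since stroke.**
- SD of entry time = (90 − 14)/√12 = 21.9 days.
- SE of the difference in arm means at 30 per arm = 21.9 × √(2/30) = 5.7 days, with a 95% range of about ±11 days.
- P(difference above 7 days) = 2 × [1 − Φ(7/5.66)] = 0.22.
- At 25 per arm the SE is 6.2 days and the probability is 0.26.

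**3. What that imbalance does to the outcome.**
- A 7-day imbalance shifts the PES–CES difference by r × 7/21.9 = 0.32r outcome SDs, which is 0.06 SD at r = 0.2 and 0.16 SD at r = 0.5.
- The 95% range of the chance shift at 30 per arm is ± r × 1.96 × √(2/30) = ±0.506r, that is ±0.10 SD at r = 0.2 and ±0.25 SD at r = 0.5.
- The pooled pretest SD is √[(127.22² + 148.46²)/2] = 138.25. In biceps RMS units the 95% range is therefore about ±14 to ±35, against a pretest difference of 167.61 − 68.17 = 99.44.

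**4. Precision recovered by adjustment.** The residual SD is multiplied by √(1 − r²). Power at 25 per group is Φ(0.8 × √(25/2)/√(1 − r²) − 1.96).

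| r | variance removed (r²) | power at 25 per group | n per group for 80% power |
|---|---|---|---|
| 0 (unadjusted) | 0% | 0.807 | 25 |
| 0.2 | 4% | 0.823 | 24 |
| 0.3 | 9% | 0.843 | 23 |
| 0.4 | 16% | 0.870 | 21 |
| 0.5 | 25% | 0.904 | 19 |

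These figures add time since stroke alone to the unadjusted test and neglect the small loss of degrees of freedom. When the baseline value of the outcome is also in the model, r should be read as the correlation that remains after it.

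**The case against.** **Validity.** A reader might infer that the wide window biases the comparison. It does not. Randomisation makes the contrast unbiased on average, the unadjusted test keeps its nominal alpha, and chance imbalance is already part of the standard error. This stands in full. Nor does it follow that the sample size is wrong: if the pretest patients covered the same window, which the article does not say, their SDs already contain this variation.

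**Size.** The primary outcomes are sEMG and EEG signals, and nothing in the article shows how strongly they depend on time since stroke. At r = 0.2 to 0.3 the gain is only about 2 to 4 points of power. The before/after change within the first session contains no 3-week recovery at all. This stands and limits the weight of the point.

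**Follow-up timing.** One might add that the 3-month visit falls inside six months of stroke for early entrants and beyond it for late ones. Table 3 schedules no sEMG or EEG at follow-up, so this cannot touch a primary outcome, and the spread applies to both arms. It does not strengthen the case.

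**Stratification.** A reader might also ask for stratified allocation. Recruitment began on 3 June 2022. Even the longest enrolment period in the article (6–8 months) ends before publication in May 2023, so allocation is very probably complete. Blocking within strata in one ward with unblinded operators would also make allocations easier to predict. The article is condensed, and its silence does not prove that allocation was unrestricted.

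**Left to an analysis plan.** Covariates are often named there. This answers the point only in part, because the article does not leave the method open: it names the between-group tests, and none of them can use the variable.

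**Conclusion.** The point holds as a matter of precision. The article records time since stroke, itself links timing to recovery, and fixes a PES–CES comparison that cannot use it. The comparison remains valid.

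Two things are given up. The first is between about 2 and 10 points of power at 25 per group and effect size 0.8, for r from 0.2 to 0.5. The second is protection against a one-off imbalance, which exceeds 1 week in about 22% of allocations and would typically move the result by a small fraction of the planned 0.8 SD. The imbalance figure rests on uniform entry times and the power figures on the assumed r. If r is near zero, little is gained. The change is worth making because the variable is already collected.

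**What to change.** Before any unblinded analysis, replace the unadjusted two-arm tests under Data statistical analysis with a prespecified model for the two patient arms: each outcome regressed on arm, the baseline value of that outcome, and days from stroke onset to randomisation (ANCOVA for continuous measures).

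The Mann–Whitney test cannot take a covariate, so name the alternative. Use an ordinal regression or a rank-based ANCOVA for graded scales such as MMT and Brunnstrom, and state what will be done for continuous measures that are far from normal. Healthy controls have no time since stroke, so comparisons with them stay outside this model. Keep the planned unadjusted tests as sensitivity analyses.

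The cost is a change of analysis wording, one degree of freedom for time since stroke and one for the baseline value. No patients or visits are added. The onset date must be available in days, because the article does not give the unit in which the duration of illness is recorded. The downside is a modest return if the correlation turns out to be low.
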